### Concealment of allocation, blinding and protection against bias

Baseline data will be obtained prior to randomisation. Randomisation will be performed centrally and allocation will not be revealed to the participants who will have been informed that the trial is comparing two forms of web-based education for diabetes (a simple/straightforward version vs. a more detailed/complicated version). Practice nurses will be provided with similar looking booklets for both comparator and intervention websites. There are potential problems with contamination (e.g. two members of the same household being randomised to different interventions with individual randomisation but cluster randomisation has greater potential to introduce bias by affecting GP behaviour (which patients they refer to the trial) and patient behaviour (participation). We will monitor the extent to which contamination occurs by determining the proportion of participants who had contact with another trial participant with a different treatment allocation.

The risk of bias in collection of follow-up data will be minimised by using standardised data collection instruments with participants completing self-assessment questionnaires before seeing the nurse to record clinical data. Clinical data will be collected by research nurses who will be trained to adhere to detailed SOPs developed in collaboration with PRIMENT CTU. Follow-up data will be collected by different nurses to those who undertake the baseline visits and training. Nurses collecting follow-up data will be blind to allocation. Blood pressure will be recorded using automated electronic sphygmanometers.

### Adherence and loss to follow-up

Fidelity of the intervention will be promoted through training practice nurses and provision of detailed SOPs to guide how nurses introduce participants to the intervention. Use of the intervention and comparator websites will be recorded automatically.

Every effort will be made to promote follow-up which will be co-ordinated by the trial manager centrally. At each follow-up point (3 and 12 months) participants will be sent up to two automated emails containing an embedded hotlink to the follow-up questionnaires. Non-responders will be sent an additional (third) personalised email from the trial manager, explaining how important follow up data are for the study, and the link will also be resent. After this, participants are sent a letter through the post, containing both the link and pencil-and-paper versions of the questionnaires with a stamped addressed envelope for returning it, in case participants prefer to complete the questionnaires offline. Finally, the trial manager will contact the patient by phone to explore reasons for non-response, encourage response, and if necessary, ask the patient to complete the PAID verbally over the phone.

Practice nurses are reminded of the need to offer participants follow-up appointments and to complete the Case Report Form (CRF) for clinical and health economic data.

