### Randomisation

Randomisation will be performed only after all baseline data collection has been completed. Randomisation will be at the level of the individual participant. It will be stratified by recruitment centre and will be performed centrally using a web-based randomisation system provided by an independent contractor (Sealed Envelope http://www.sealedenvelope.com/). This system will send an email to the trial manager when a patient has been randomised detailing which arm the patient has been allocated to. This will then be forwarded to the nurse who will be introducing the control and intervention websites to the patients in visit 2.

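### The trial manager is sent every allocation and also chases non-responders and may take the co-primary PAID by phone; no section blinds that role.

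*Protocol article*

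**What the plan says.** Two sections of the protocol article give tasks to the same role.

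- **Randomisation.** "This system will send an email to the trial manager when a patient has been randomised detailing which arm the patient has been allocated to". On the next step the article says: "This will then be forwarded to the nurse who will be introducing the control and intervention websites to the patients in visit 2".
- **Adherence and loss to follow-up.** "Every effort will be made to promote follow-up which will be co-ordinated by the trial manager centrally". The sequence applies at both follow-up points: "At each follow-up point (3 and 12 months) participants will be sent up to two automated emails", then a personalised email from the trial manager, then a postal pack with paper questionnaires. The last step is a call: "Finally, the trial manager will contact the patient by phone to explore reasons for non-response, encourage response, and if necessary", "if necessary, ask the patient to complete the PAID verbally over the phone".

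The section on concealment, blinding and protection against bias masks two groups. Participants are not told their arm, hear the trial described as a comparison of two forms of web education, and get similar-looking booklets. For assessors it says: "Nurses collecting follow-up data will be blind to allocation". Self-reported outcomes are further protected by standardised instruments that participants fill in before they see the nurse. Primary outcomes names PAID as a joint primary outcome with HbA1c.

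**The concern.** The plan takes trouble to separate knowledge of allocation from data collection. Each practice must supply two staff so that one can stay blinded, and different nurses collect the follow-up data. That separation protects HbA1c, a laboratory value. At the phone step the subjective co-primary does not have it, because the role that makes the call is the role that was sent the allocation.

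Two things are exposed. The first is the recorded score: a spoken answer to a caller who can know the arm may be affected by tone or prompting, in either direction. The second is who is observed: the personalised email and the effort put into calls also rest with someone who can know the arm.

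PAID is tested at 5% in its own right, so a bias in PAID alone can affect a primary conclusion. The 3-month calls also matter, because the Analysis section uses 3-month data to impute missing 12-month values.

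**Working it through.** **1. Who knows, who collects, who is blinded.**

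| Role | Sent the allocation? | Collects follow-up data? | Stated to be blind? |
|---|---|---|---|
| Introducing nurse | Yes, forwarded by email | No, different nurses do this | No |
| Follow-up nurse | No | Clinical data, including blood for HbA1c | Yes |
| Participant | Not told | PAID and other questionnaires, self-completed | Yes |
| Trial manager | Yes, every participant | PAID by phone, last resort | Not stated |

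Only the trial manager both holds allocations and may collect a primary outcome. The article does not hand the calls to anyone else or restrict access to the allocation emails. The Abstract's statement about blinded practice nurses is not contradicted, since it covers clinical data only.

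**2. The plan's own precision for PAID.** Inputs from Sample size: effective SD 10.75, target difference 4.0, at least 300 analysed, 5% level. Equal allocation (150 per arm) and a two-sided test are my assumptions.

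- SE of the difference = 10.75 × √(2/150) = 1.24.
- Power = Φ(4.0/1.2413 − 1.96) = Φ(1.262) = 89.7%, which reproduces the stated 90%.
- For HbA1c, SE = 0.676 × √(2/150) = 0.0781 and power = Φ(0.25/0.0781 − 1.96) = 89.3%, also in line.

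No stated figure is in dispute.

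**3. What a phone effect could do.** Let *p* be the share of PAID scores taken by phone (the same in both arms) and *d* the between-arm shift in those scores caused by the caller. The documents give neither, so the values below are assumptions.

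- Bias in the mean difference = *p* × *d*.
- Type I error = 1 − Φ(1.96 − bias/SE) + Φ(−1.96 − bias/SE).

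| Phone share *p* | Shift *d* (points) | Bias (points) | Share of 4.0 target | Type I error |
|---|---|---|---|---|
| 5% | 2 | 0.1 | 2.5% | 5.1% |
| 10% | 4 | 0.4 | 10% | 6.2% |
| 20% | 4 | 0.8 | 20% | 9.9% |

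Last row in full: 0.8/1.2413 = 0.644; 1 − Φ(1.316) = 0.094; Φ(−2.604) = 0.005; the sum is 0.099.

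The table covers only a shift in the recorded scores. Unequal chasing cannot be sized from the documents.

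**The case against.** The strongest reply is that PAID is self-reported. The participant is the assessor, the participant is masked, and the instrument has 20 fixed items. What remains is interviewer influence, and only for those who answered neither the emails nor the postal pack. The reminder sequence is the same for every non-responder and its first steps are automated, so no arm-dependent discretion is described. The call also reduces missing PAID data, which is itself a source of bias. Finally, the article says that SOPs will cover data collection and promises further sensitivity analyses for bias, so the mode of completion may be dealt with there.

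Most of this stands, and it limits the size of the problem. It does not remove it. Participant masking does not stop a caller who knows the arm from influencing a spoken answer. A fixed sequence still leaves the wording of the personal email and the persistence of the calls to the person who makes them. The lack of mode-of-completion detail is not counted against a condensed article; the point rests on the article itself giving both tasks to one role.

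A reader might go further and infer that PAID is collected unblinded in general, that its false-positive rate is badly inflated, or that the caller has a stake in the programme. The documents support none of these. Self-completion is the main route. Large inflation needs large inputs: 20% by phone with an 8-point shift would give 1.6 points of bias and about 25% type I error, but that shift is twice the target effect. The article says that its authors developed the programme, but it does not say that the trial manager was one of the developers.

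**Conclusion.** The point holds as a gap in assessor blinding for a contingent part of one joint primary outcome. As written, any PAID score taken by phone is taken by someone who was sent the participant's arm. HbA1c is not affected.

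The size is unknown and may be negligible. Under the illustrative assumptions the bias runs from 0.1 to 0.8 PAID point and the type I error from 5.1% to 9.9%. These figures rest on assumed phone shares and shifts, equal allocation, 150 analysed per arm and the plan's SD. They do not show that bias will occur, and the documents do not show that chasing would differ by arm. The case for acting is that the gap is avoidable at little cost and that mode of completion is hard to reconstruct afterwards.

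**What to change.** **Preferred.** Have the randomisation system email the allocation directly to the introducing nurse, who receives it anyway, and keep the trial manager without access to allocations. The manager can then go on sending the personalised email and making the calls. Keep the phone step, because it reduces missing PAID data.

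**If the manager must hold allocations.** Have an existing team member without access to them make the personalised contacts and take the PAID by phone. The documents do not show whether such a person is available.

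**Under either option.** Record the mode of PAID completion at 3 and 12 months, report the phone share by arm, and add a sensitivity analysis that treats phone-collected PAID as missing. This is still useful with a blind caller, because a participant may reveal the arm during the call.

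**Cost.** A change of email recipient, an SOP line, loss of the manager's central relay of allocations, and a little more analysis. The preferred option needs no extra participants, visits or staff.

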### Sample size

We hypothesise that use of the intervention will improve both PAID scores and HbA1c. The analyses will gain power through adjustment for baseline levels. We have back-calculated the relevant effective standard deviations (SDs) from a previous trial as 0.676 for HbA1c and 10.75 for PAID, substantially lower than the SDs of cross-sectional measures of around 1.4 and 16 respectively because of the correlation between baseline and subsequent measures. We intend to recruit 350 participants; with attrition of up to 15 % we anticipate at least 300 patients for the primary analysis. This will give us 90 % power of detecting at a 5 % significance level a true average difference in the PAID score of 4.0 and 0.25 % change in HbA1c. These are both small effect sizes. Since HbA1c and PAID are joint primary outcomes measuring very different aspects of T2DM both will be tested at a 5 % significance level. Results from both outcomes will be presented side-by-side in any publication irrespective of their statistical significance. This follows similar practice in other trials in this area [21].

### Analysis

The analysis will follow a pre-specified analysis plan based on comparing the groups as randomised (intention-to-treat). Follow-up HbA1c will be adjusted for initial levels and other baseline covariates including age, gender, centre, participation in other self-management programmes, pre-existing cardiovascular disease and duration of diabetes. PAID and other outcome measures will be analysed similarly. Sub-group analysis will be undertaken by baseline glycaemic control and duration of diabetes, treating all potential effect modifiers as continuous. For the purpose of presentation, results will be shown for those with good vs. poor baseline glycaemic control (HbA1c 7.5 % or greater vs. 7.4 % or less). Missing follow-up data will be multiply imputed where possible using other outcome data (e.g. 3 m data when 12 m data are missing) and other sensitivity analyses investigating the potential for bias undertaken.

The amount of use the intervention receives (e.g. number of log-ins) will be further investigated as a potential mediator for efficacy. Using instrumental variable methods with randomisation as the instrument, an unbiased estimate of the average causal effect of the intervention on the primary outcomes (HbA1c and PAID) will be obtained in a subgroup who would use the intervention a certain amount [22].

If contamination (where members of the control group have access to the active intervention e.g. through a family member in the intervention group) does occur it will be dealt with in the analysis by:Our main (primary) analysis will be a full intention-to-treat analysis on the whole trial populationWe will report the extent of any contaminationWe will undertake a sensitivity analysis using non-contaminated controls in the control arm only. However as this loses the benefits of randomisation we will alsoUndertake a Complier Average Causal Effect (CACE) analysis which respects randomisation. For this CACE analysis we would label contaminated control participants as potential non-compliers [23].

### Economic analysis

#### Incremental cost-effectiveness

The determination of within-trial incremental cost-effectiveness of facilitated access to HeLP-Diabetes compared to usual care for patients with T2DM will follow NICE guidance by adopting both a health and personal social services and a wider public sector resource perspective [24, 25]. The components of the analysis are health outcomes, costs of the active and control intervention, and the potential impact on diabetes care and complications. QALYs will be calculated using area under the curve analysis from the baseline, 3- and 12- month follow-ups, adjusting for baseline levels. Intervention costs will be measured directly. NHS and social care costs will be calculated from the self-reported usage data collected from patients and the data extracted from the electronic medical record by nurses.

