### Intervention

The intervention consists of facilitated and supported access to HeLP-Diabetes. There are three components to the supported access: first an introductory session, secondly supportive follow-up phone calls, and thirdly, on-going discussion of patient’s self-management goals in routine appointments for diabetes-related matters.

In the introductory session practice nurses will give the patient a booklet containing the uniform resource locator (URL) for the programme, the participant’s log in details, and information about the content of the website and how best to use it. Nurses will show the patient how to access the website, and introduce them to the main content areas. The nurse will discuss with the patient what the patient’s most pressing needs are and use this to guide the patient toward certain sections (for example, improving diet, being more physically active, or managing emotions). Follow-up phone calls will be offered to support the patient in use of the programme. Nurses and doctors in participating practices will be encouraged to refer to the programme in consultations with participating patients and to integrate information from the programme into management plans.

HeLP-Diabetes is a web-based programme with multiple components. There are information sections  including how diabetes is treated, possible complications of diabetes, possible impacts of diabetes on relationships at home and at work, dealing with unusual situations like parties, holidays, travelling or shift work, and what lifestyle modifications will improve health. There are sections addressing skills and behaviour change, including behaviour change modules on eating healthily, losing weight, being more physically active, smoking cessation, moderating alcohol consumption, managing medicines, glycaemic control and blood pressure control. These all include motivating information on the benefits of behaviour change, self-assessment quizzes for patients to assess whether and how much they need to change, and opportunities for goal-setting and self-monitoring. The third strand of components focuses on emotional well-being and contains self-help tools based on cognitive behavioural therapy and mindfulness. There are multiple personal stories (used with license from healthtalk.org), and a moderated forum for users to interact with each other.

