### Comparator

From an NHS perspective the important research question is whether the proposed intervention can improve health outcomes when compared to current practice. However, to improve acceptability to participants and help maintain blinding, all participants will have access to a website. Participants in the control arm will have access to a simple information website, based on the information available on the Diabetes UK and NHS Choices websites. These participants will also be given a booklet with the URL and user log in details, and will also have the introductory session with the nurse explaining how to use the website and offer of follow-up phone calls. However, as the website will have no behaviour change components, no emotional support and only simple information, it is unlikely that there will be many opportunities to refer to it in diabetes-related appointments.

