#### Costs of the intervention

Costs of the intervention to the NHS are made up of two major components: development of the intervention and facilitation/implementation costs. The resources required for the development of the intervention will be monitored during the development process. Once the intervention has been developed it will need ongoing maintenance and updating; these costs will be recorded. The economic evaluation will include the maintenance and hosting costs, with research costs separated from treatment costs. Development costs will be considered sunk costs and not included in the analysis as these would not be incurred if the intervention were rolled out in practice.

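### The cost-effectiveness analysis names usual care as its comparator, but no arm receives usual care, and facilitation costs shared by both arms will partly or largely net out

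*Protocol article*

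**What the plan says.** Under *Incremental cost-effectiveness*, the protocol article sets out to determine the "within-trial incremental cost-effectiveness of facilitated access to HeLP-Diabetes compared to usual care for patients with T2DM". The same paragraph lists the costs of both the active and the control intervention among the components of the analysis.

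The *Comparator* section says that the question that matters to the NHS is "whether the proposed intervention can improve health outcomes when compared to current practice". It then departs from that comparison: "However, to improve acceptability to participants and help maintain blinding, all participants will have access to a website". The control condition follows: "Participants in the control arm will have access to a simple information website". Controls also get a booklet with log-in details, and they "will also have the introductory session with the nurse explaining how to use the website and offer of follow-up phone calls".

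For the intervention arm, the *Intervention* section says: "There are three components to the supported access: first an introductory session, secondly supportive follow-up phone calls". The third component is continuing discussion of self-management goals in routine diabetes appointments.

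Under *Costs of the intervention*, NHS costs are "made up of two major components: development of the intervention and facilitation/implementation costs". The section then says: "Development costs will be considered sunk costs and not included in the analysis". Maintenance and hosting are included. *Facilitated access and implementation costs* says that the help given to each patient and professional will be recorded and costed, and that the data will feed a model for a typical Clinical Commissioning Group.

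**The concern.** A within-trial analysis can estimate only the contrast between the randomised arms. Here that contrast is facilitated HeLP-Diabetes against a facilitated information website. The article labels it as a contrast with usual care, which its own Comparator section treats as something different.

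The label affects both halves of the ratio:

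- **Costs.** With development excluded, facilitation is the one of the two named major components that remains. Part of it is also delivered to controls. Subtracting control costs removes that part, although a health service moving from usual care to HeLP-Diabetes would pay it in full.
- **Effects.** If the control package has any benefit, the measured QALY gain is not the gain over usual care.

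Cost-effectiveness is one of the trial's two stated aims. A commissioner who takes the label at face value would read the ratio as the answer to the NHS question, which the analysis as described does not give.

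**Working it through.** The protocol article states no unit cost, facilitation time or expected QALY gain, so there is no figure of the plan's own to reproduce. The check compares the arms item by item and then puts the consequence in symbols.

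**Step 1: what each arm receives** (Intervention and Comparator sections)

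| Item | HeLP-Diabetes arm | Control arm | Usual care, as the Comparator section implies |
|---|---|---|---|
| Website | multi-component programme | simple information site | none supplied by the trial |
| Booklet with log-in | yes | yes | no |
| Introductory nurse session | yes | yes | no |
| Follow-up calls | offered | offered | no |
| Goal discussion in routine appointments | yes | few opportunities expected | no |

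Two of the three supported-access components are given or offered to controls. The third is largely not mirrored.

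**Step 2: costs.** Let F be the facilitation cost per person in the HeLP-Diabetes arm and c the share of F that is also incurred per control. If both arms are costed, incremental facilitation cost = F × (1 − c). Against usual care it would be F. The documents fix neither F nor c. Taking F = 100 units as an assumption:

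- c = 0: 100 × (1 − 0) = 100
- c = 0.5: 100 × (1 − 0.5) = 50
- c = 0.8: 100 × (1 − 0.8) = 20
- c = 1: 100 × (1 − 1) = 0

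The value c = 0 applies only if control facilitation is left uncosted. The value c = 1 needs identical facilitation in both arms, and Step 1 shows that the arms differ. With both arms costed, c lies somewhere between, so facilitation nets out in part, possibly in large part. The cost of running the control website is netted off in the same way.

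**Step 3: the ratio.** Let ΔC and d be the incremental cost and QALY gain between the randomised arms, both taken as positive. Let G be the cost of the control package (website, session, calls), and e the QALY gain of that package over usual care, taken as zero or more. Any effect of the package on other NHS costs is ignored.

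- Ratio as analysed: ΔC / d
- Ratio against usual care: (ΔC + G) / (d + e)

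The second exceeds the first when d × (ΔC + G) > ΔC × (d + e), that is, when d × G > ΔC × e.

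If e = 0, any positive G means that the analysed ratio is too low. If e is large enough, the inequality reverses. The trial measures G, ΔC and d but cannot measure e. The cost side is therefore understated, while the net direction for the ratio is undetermined.

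**The case against.** The strongest reply is that the mismatch in labels is real but little follows from it. Several parts of that reply stand.

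- A reader might infer that facilitation cancels altogether, leaving an increment of about zero. The documents do not support this. The third support component is not mirrored, call uptake and length may differ, and the nurse's introduction to HeLP-Diabetes includes guiding the patient by need. Individual help is recorded, so differences between the arms can be measured.
- A reader might infer that the ratio leaves out most of what the NHS would pay. That is not shown either. The list of economic outcomes also includes staff training, supported access, and maintaining and updating the programme.
- The Comparator section gives trial reasons for the control website, and the sentence on maintenance and hosting separates research from treatment costs. Control facilitation could perhaps be treated as a research cost and not subtracted. But that sentence does not mention control facilitation, and the economic section counts control intervention costs. Even on this reading, gross costs would be paired with effects against an active control, which would have to be stated.
- The commissioning-group model may already use gross costs. Nothing says that it nets off the control arm, so it cannot be called wrong, only unclear.

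It might also be said that economic scenarios belong in a fuller analysis plan that is not shown. That is fair for detail. It does not cover a comparator that the article states and that its own description of the control arm contradicts.

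**Conclusion.** The point holds as a misnamed comparator with a real but unquantified consequence. The within-trial analysis compares HeLP-Diabetes with a facilitated information website. If control costs are counted as the economic section lists them, the shared introductory session and calls net out partly or largely. The incremental intervention cost is then understated as a measure of what the NHS would pay over usual care.

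A reader might go further and conclude that the ratio is too favourable by some sum per QALY. The documents do not allow that. They give no costs and no QALY gain, and the gain over usual care may exceed the gain over the information website, which would pull the ratio the other way. The conclusion on cost rests on one assumption: that control facilitation is costed and subtracted, which is the plain reading of the text. The conclusion on labelling needs no assumption.

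**What to change.** 1. In the economic section, name the base-case comparator as facilitated access to a simple information website.
2. Pre-specify one usual-care scenario in which the control website, introductory session and call costs are set to zero. State beside it that its effects remain those against the information website. It therefore assumes that the control package changes neither QALYs nor other service use relative to usual care.
3. State that the commissioning-group model uses gross facilitation costs, not costs net of the control arm.

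The cost is a change of wording and one extra scenario. The article already plans to record individual help and staff time, so trial conduct does not change. The downside for the sponsor is that the usual-care scenario may show a less favourable ratio than the base case. The scenario also remains a hybrid of usual-care costs and effects against the website, and it should be reported as such.
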